### Randomization

Participants who will provide written consent to participate in this clinical trial will be given numbers in the order of their Informed Consent Form submission, and will undergo screening as scheduled. The screening number is a five-digit code. The first digit is the letter S, which stands for “screening.” The second digit contains the institution code, and the last three digits are determined according to the order of consent submission. After selecting appropriate participants based on the inclusion and exclusion criteria, we will give each participant a consecutive participant identification number. The participant identification number consists of five digits. The first digit is the letter R, which stands for randomization. The second digit contains the institution code, and the last three digits are determined according to the order of consent submission. Examinees will apply the participant identification numbers to a randomization table provided by a third-party statistician, and will conduct the medication adherence monitoring method.

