### Study design

This study has a multicenter, open-label, prospective, randomized controlled trial (RCT) design. One hundred fourteen KTRs who fill out the Informed Consent Form are registered and randomized 1:1 into the ICT-based centralized clinical trial monitoring group (*n* = 57) or the ambulatory follow-up group (*n* = 57). The planned follow-up duration is 6 months (Fig. 1). The ICT-based centralized clinical trial monitoring group is given a smart pill box equipped with a personal identification system. Fingerprint registration is required in advance, so that it would be used for authentication before each use of the smart pill box later. The adherence-related information obtained from the pill box is saved, monitored, and sent out via a home monitoring system. Of the home monitoring system data, those necessary for the clinical trial are extracted and incorporated into the electronic Case Report Form (eCRF) system. All data is consolidated and managed within the comprehensive clinical trial management system (CTMS). In the ICT-based, centralized clinical trial monitoring group, feedback is sent to both patients and medical staff in the form of texts and pill box alarms if there is a dosage/dosing time error or a missed dose.

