### Sample size

We hypothesized that the ICT-based centralized monitoring group would be superior to the control group in terms of dose-taking compliance. A one-tailed test with a 0.05 significance level and 80% power provided a size of 51 in each group. With an estimated 10% dropout, the final sample size of 57 was determined (a total of 114 subjects, 57 in each group).

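### The published randomisation procedure lets anyone holding the table foresee the next arm before eligibility is decided, and its two numbering rules for randomised patients conflict.

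*Protocol article*

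**What the plan says.** All references are to the protocol article.

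- **Study design.** "This study has a multicenter, open-label, prospective, randomized controlled trial (RCT) design". Patients are "registered and randomized 1:1 into the ICT-based centralized clinical trial monitoring group" or to ambulatory follow-up, 57 in each.
- **Randomization, before screening.** Consenting patients "will be given numbers in the order of their Informed Consent Form submission, and will undergo screening as scheduled". The screening number is the letter S, an institution code and three digits.
- **Randomization, after screening.** "After selecting appropriate participants based on the inclusion and exclusion criteria, we will give each participant a consecutive participant identification number". This number is the letter R, the institution code and three digits. For these digits the section uses the same rule as for the screening number: "the last three digits are determined according to the order of consent submission".
- **Randomization, allocation.** "Examinees will apply the participant identification numbers to a randomization table provided by a third-party statistician". The same sentence has these people carry out the adherence monitoring.
- **Study participants.** The last exclusion criterion covers any other reason for which the investigators judge participation inappropriate.

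**The concern.** Randomisation protects against selection bias only if whoever decides on a patient's entry cannot know which arm comes next. Here the sequence of numbers is known in advance, the arm is found by looking a number up in a supplied table, and the people doing the look-up also appear to run the intervention. The independent statistician is described only as the source of the table.

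If the table can be read early, a patient expected to adhere poorly, or to cope badly with the device, can be judged unsuitable when one arm is next and accepted when the other is. The primary outcome is adherence, which depends on patient characteristics that staff can partly judge at screening. The Statistical analysis section compares adherence between arms with a t test, which cannot remove an imbalance created at entry.

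Separately, if the two numbering rules differ, two sites could match patients to lines of the table in different ways.

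**Working it through.** The question is one of sequence and logic, so the steps are set side by side. The plan's only related figure is checked first.

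**1. Sample size.** The Sample size section states "A one-tailed test with a 0.05 significance level and 80% power provided a size of 51 in each group" and assumes 10% dropout. 51 / (1 − 0.10) = 56.7, rounded up to 57; 2 × 57 = 114. This agrees with the article. The section gives no effect size or SD, so it offers no scale on which to express a bias.

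**2. Order of steps.** Consent and S-number; screening; selection on the criteria; R-number; look-up in the table. The R-number is thus formally issued after the eligibility decision. What matters is whether it can be known sooner.

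**3. Is the R-number foreseeable?**
- *Digits follow consent order.* The R-number has the same site code and sequence rule as the S-number, so it is known at consent, before screening.
- *Digits run consecutively among selected patients.* The next R-number is the next unused one at that site, known before the next patient is judged.

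It is foreseeable on either reading.

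**4. Does a foreseeable number mean a foreseeable arm?** Only for someone with access to the table. With access, the next arm is known with probability 1; under concealed simple 1:1 allocation it would be 0.5. The section describes no sealed envelopes, central release or other step that withholds the table until eligibility is recorded.

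**5. Do the two numbering rules agree?** Illustration: at institution 1, three patients consent as S1001, S1002 and S1003, and the second fails screening.

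| Rule | First patient | Third patient | Line 2 of the table |
|---|---|---|---|
| Consent order | R1001 | R1003 | skipped |
| Consecutive after selection | R1001 | R1002 | used |

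The third patient is matched to different lines and may receive a different arm. If the R-digits are the consent number, as the identical rule for the S-number suggests, the rules agree only when every consenting patient is eligible and patients are randomised in consent order. A looser reading, numbering eligible patients without gaps but by date of consent, skips no lines but still needs randomisation in consent order.

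**6. Do skipped lines matter for power?** Very little. Taking a split of 62 and 52 purely as an assumption, the effective size per arm is 2 × 62 × 52 / 114 = 56.6, against 57. The numbering conflict is about clear, auditable allocation, not lost power.

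**The case against.** The strongest reply is that the article never says the table is open, held at sites or readable before enrolment. It says a third party provides it, and places both the R-number and the look-up after selection, which is the protective order. A predictable serial number is normal and harmless if the list is concealed. Who holds the list is the kind of detail a condensed article leaves to the full protocol, which is not shown; nor is the SPIRIT checklist that the article cites.

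Three further points are fair:

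- The word Examinees literally means those examined; reading it as staff is an inference. It is supported by their conducting the monitoring, and patients consulting the table would be no better concealed.
- An investigator catch-all exclusion is routine and matters only if the list is visible. Patients who refuse the monitoring system are excluded whatever the arm, which removes one motive for steering.
- Lines are skipped only on the consent-order reading, and the repeated sentence may be a drafting slip.

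All of this stands, and it limits the point to what the procedure permits. It does not dispose of it. The article describes the procedure down to single digits and says who does the look-up, so the weakness lies in a stated mechanism and not in silence. If a safeguard exists, the section misdescribes the trial; if none exists, the procedure needs changing. Nor does the reply resolve the conflict between the numbering rules.

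**Conclusion.** The point holds in conditional form. As published, the procedure permits anyone holding the table to foresee the next arm before deciding eligibility, in an open-label trial with an open-ended exclusion. This rests on two assumptions: that Examinees are trial staff, and that no unpublished step withholds the table. The conflict between consecutive numbering and consent-order digits needs neither assumption and must be reconciled in any case.

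A reader might infer that allocations were actually foreseen, or that sites hold an open list. The article does not say so. A reader might also want the bias expressed as a share of the planned effect or as an inflated type I error. Any such figure would only return the assumed effect, SD and share of steered patients, none of which the article states. Likewise, the size of any departure from 57:57 through skipped lines depends on a screen-failure rate that is not given, and its effect on power would be small. No quantified bias is claimed.

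**What to change.** 1. Keep the list with the third-party statistician, or inside the trial management or electronic case report form system that the trial already runs, out of reach of staff who recruit or assess eligibility.
2. Release one allocation at a time, only after eligibility has been confirmed and recorded.
3. Number randomised patients in order of randomisation within site. Keep consent order for the screening number only.
4. Reword the Randomization section to match: name the role that requests the allocation in place of Examinees, and state who holds the list and when each line is released.

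The cost is a small system set-up and a text change. If a concealment step is already in use, only the text needs changing. The sample size stays at 114.

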### The ICT-based centralized clinical trial monitoring system: components and information to be collected

The ICT-based centralized clinical trial monitoring system consists of (1) a personal identification system, (2) a smart pill box to obtain drug adherence data, (3) a home monitoring system to save, monitor, and transmit the received data, (4) the eCRF system that selects and prepares from the home monitoring system that data necessary for the clinical trial, and (5) the comprehensive CTMS that consolidates and manages all relevant data (Fig. 3). The information obtained via the smart pill box includes whether a dose is taken or not, dosage and remaining pill counts, dosing time, and alarm times and frequency.

**Fig. 3 Fig3:**
[figure not shown]
ICT-based centralized clinical trial monitoring system. *CTMS* clinical trial monitoring system, *eCRF* electronic Case Report Form, *ICT* information and communication technology

### Smart pill box

Information measured by smart pill boxes:Medication use: the system checks whether or not the patient has ingested medications according to the clinical trial protocol and a schedule prescribed by the researchersDoses of medications ingested and doses of medications remaining: the system checks the doses of medications ingested and the doses of medications remainingDosing time: the system records the actual time at which the participant ingested medicationsAlarm time: the system records alarm times and the number of alarms set according to the patent’s medication usage

Device details:Product license number: N/AProduct name: smart pill boxModel name: smart pill boxManufacturer: Jeyun Medical Co.Pharmacokinetics and properties:Contains drugs in various forms including powder paper, capsule, and bottleAn automatic multi-media alarm feature that sets off the alarm according to the drug administration schedule, autonomic storage feature, and medication counseling featureA sensor that measures the amount of leftover medications and a feature that monitors drugs that are placed inside or taken out of the smart pill boxMedication use instructions for when patients are outside. Patients can check the amount of remaining medications inside their smart pill boxes to the smallest unitAn alarm for missed dose, misuse, or overuse of medicationsAn electronic switch on the storage space, and emergency switchingAutomatic formation of a database of prescribed drug administration schedulesRemote, real-time monitoring and control of the functional and technical conditions of the smart pill boxA data transfer feature (provides interfaces for WPAN, LAN, WLAN, and WAN modems)—Bluetooth, Ethernet, WiFi, 3G/4G modem interface, etc.
Shape/structure and sizePower: DC 12 V/3 A or lessOverall size (L–W–H): 289 × 141 × 136 (mm)/storage size (L–W–H): 206 × 105 × 74 (mm)Maximum capacity: 1.0 kgDisplay: TFT Touch LCD 3.5 inch, 320 × 240Total weight: < 1.57 kgOperating temperature: 0–70 °CMain processor: ARM7 900 MHz Quad-core, 1 GB RAMInternal memory: 8 GB, network: 10/100 Mbps Ethernet-supported, USB 2.0 4 port-supportedMain OS (operating system): Debian, automatic firmware upgrade supported, GUI (Graphical User Interface)-based operating system

### Home monitoring system

The home monitoring system will accumulate data about medication adherence measured from the smart pill boxes for each participant registered through the integrated management system, and will send them to the eCRF according to a defined transfer format. Moreover, when any of the situations defined in the clinical trial protocol arise, a defined feedback is sent to the patient and medical staff. The process of data transfer with the home monitoring system is summarized below;The home monitoring system receives user information (personal information, screening number, etc.) from the integrated management systemThe home monitoring system/integrated management system transfers information necessary for setting the pill box to the drug administration management platform implemented on the CTMSThe drug administration management platform sends information necessary for the pill box to set the drug administration informationResults of drug administration are sent to the home monitoring server systemThe drug administration management platform on the home monitoring system/CTMS sends the user’s drug administration information through the home monitoring server systemThe home monitoring server system sends the information to the eCRFFeedbacks are sent to the patient’s cell phone

### The ICT-based centralized clinical trial monitoring system: feedback

In the ICT-based centralized monitoring group, both subjects and medical staff receive feedbacks regarding a missed dose, misuse, and overuse of the medication in the form of a text message alarm. In case of a missed immunosuppressant dose, the first violation generates a feedback within 1 h at the break of the ± 3-h range from the fixed dosing time. Up to two additional texts are sent at an interval of 30 min if the dose is still not taken after the feedback. For any discrepancy between the dosage taken and the dosage prescribed, a feedback is sent within 1 h from the moment of recognition. Similarly, if a dose is taken outside of the allowed ± 3-h dosing time range, a feedback is sent within 1 h of recognition. To minimize reminder fatigue, we limited additional alarms after the first feedback to two times. Any additional alarms after the two reminders will be sent to the patient’s family. Medication use information of KTRs is sent to the home monitoring system and the eCRF system in real time to allow the medical staff to check on the patients’ medication use, dosing time, and dosage. Through the eCRF system, medical staff can gain insights into all patients’ daily history of medication use, and all patients’ or a single patient’s monthly history of medication use.

### Control group

Participants in the control group will also record their daily medication use, undergo an adherence evaluation at every visit, undergo clinical laboratory and immunological tests, and have their blood levels of immunosuppressants measured.

### Questionnaires

Participants in both groups will complete the Modified Morisky Adherence Scale [13] and the Belief about Medicine Questionnaire—general (BMQ-G) [14]. We aim to investigate the patients’ level of trust on their prescriptions and their perception of medication use.

### Primary outcomes

The primary outcome in this trial is adherence to medication. Both in the ICT-based centralized clinical trial monitoring group and the control, pill counts are done at 4, 8, 12, 16, 20, and 24 weeks of follow-up. Multiple items of adherence – dose-taking compliance, dose-frequency compliance, dose-interval compliance, and drug holidays – are assessed based on the smart pill box data in the ICT-based centralized monitoring group and the drug administration diary in the ambulatory follow-up group, respectively. In the ICT-based centralized monitoring group, three types of immunosuppressants—tacrolimus, mycophenolic acid, and steroids—are placed in a single bag, which is then placed inside a smart pill box. The patient’s medication usage is assessed based on the perceived weight of the leftover medications in the bag. On the basis of this weight information, we can identify the type and dose of medications that the patient has ingested, and calculate the adherence. Each item of adherence is listed below [15]:Dose-taking compliance = the number of pills taken over a certain time period/the number of pills prescribed over the same period × 100%Dose-frequency compliance = the number of days of correct daily dosing frequency over a certain time period/the number of days over the same period × 100%Dose-interval compliance: the number of correct dosing interval over a certain time period/the number of days over the same period × 100%.A correct dosing interval is defined with a ± 25% margin (in this trial, medication is taken twice a day, with a dosing interval of 12 h. Allowed dosing interval is thus ranged from 9 to 15 h)Drug holidays = the number of days without dose taking/the number of days over the same period × 100%Medication possession ratio = the sum of the days’ supply for all fills of a given drug in a particular time period/the number of days in the time period × 100%

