### Statistical analysis

For categorical data, percent (%) is used for the number of subjects in a category against the total number of subjects. Analysis of categorical data uses the chi-square test or Fisher’s exact test. For continuous data, descriptive statistics (mean and standard deviation (SD)) are given, and the *t* test and the Mann-Whitney *U* test are used for analysis of normal distribution data and non-normal distribution data, respectively. The inter-group difference in adherence to immunosuppressants is assessed with the *t* test. Summary statistics of mean, SD, median, minimum value, and maximum value are presented for measurement data at each visit. The intra-group variation is analyzed with the paired *t* test or Wilcoxon’s signed rank test. Multivariate analysis is performed to identify clinical factors associated with drug compliance. Statistical significance is obtained with a *P* value of < 0.05.

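### The protocol does not say which adherence item decides the trial: the primary outcome has four items of equal standing, but the hypothesis and sample size concern dose-taking compliance alone.

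*Protocol article*

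**What the plan says.** Three sections of the protocol article bear on the point.

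- **Primary outcomes.** "The primary outcome in this trial is adherence to medication". The items assessed are "dose-taking compliance, dose-frequency compliance, dose-interval compliance, and drug holidays". None is called the main one, and no rule combines them. The list of formulas that follows has five entries. The extra one begins "Medication possession ratio = the sum of the" and is not among the four items named in the text.
- **Sample size.** The hypothesis is that the monitored group will be "superior to the control group in terms of dose-taking compliance". A one-tailed test at 0.05 with 80% power gives 51 per group, raised to 57 for 10% dropout. No other adherence item appears here.
- **Statistical analysis.** The group difference in adherence is assessed with a t test, without naming an item. The general rule is "Statistical significance is obtained with a *P* value of < 0.05". No order of testing or adjustment is given, and the sidedness of this threshold is not restated.

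The Secondary outcomes section contains none of the adherence items, so nothing there gives any of them a lower rank.

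**The concern.** The section that defines the primary outcome and the section that sizes the trial do not name the same thing. One gives a domain with several items of equal standing; the other gives one item. A claim of success on dose-frequency compliance, dose-interval compliance or drug holidays could be defended from the Primary outcomes section even if dose-taking compliance showed no difference.

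Two things are at stake. The first is the error rate of the primary claim, which exceeds the stated 5% if any of several items may carry it. The second is the conclusion itself. The items measure different things: quantity, daily frequency, timing and whole missed days. A patient who takes every pill but at irregular hours scores fully on dose-taking and poorly on dose-interval compliance. The plan gives no rule for a trial in which the items point different ways.

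**Working it through.** **Inputs.** From Sample size: one-tailed alpha 0.05, power 80%, 51 per group, 10% dropout. From Primary outcomes: four named items, five formulas. Assumed, because the document gives none: equal pairwise correlation between the item test statistics, each oriented so that a higher value favours the monitored group (drug holidays reversed).

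**1. The plan's own figure.** 51 / (1 − 0.10) = 56.7, rounded up to 57 per group and 114 in total. The dropout step reproduces. The 51 cannot be checked forward because no effect size or SD is stated. Solved backward with the normal formula, it implies a standardised difference of (1.645 + 0.842) × √(2/51) = 0.492. All of this is for one endpoint at the full alpha.

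**2. Chance of at least one false positive if each item is tested at one-sided 0.05.** Under independence it is 1 − 0.95^k:

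- four items: 1 − 0.95^4 = 18.5%
- five items: 1 − 0.95^5 = 22.6%

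With correlation, from an equicorrelated multivariate normal simulation (1,000,000 draws):

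| Assumed correlation | Four items | Five items |
|---|---|---|
| 0.5 | 14.4% | 16.6% |
| 0.8 | 10.6% | 11.7% |
| 0.9 | 8.8% | 9.4% |

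The four-item column is the relevant one, since only four items are named as assessed.

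**3. If the threshold is two-sided.** With four items, the chance of any significant result is 15.6% at correlation 0.5 and 9.4% at 0.9. Counting only results that favour the monitored group, it is 7.8%, 5.7% and 4.7% at 0.5, 0.8 and 0.9, against 2.5% for a single item. The inflation remains, relative to the level of one test.

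**4. Cost of keeping the items co-equal.** With Bonferroni, one-sided, at the implied difference of 0.492, n per group = 2 × (z(1−α/k) + 0.842)² / 0.492²:

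| Items | Alpha each | n per group | With 10% dropout | Power on one item with 51 per group |
|---|---|---|---|---|
| 4 | 0.0125 | 79 | 88 | about 60% |
| 5 | 0.01 | 83 | 93 | about 56% |

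**5. Cost of one primary item.** Alpha stays at 0.05 and the sample size stays at 51, or 57 with dropout.

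**The case against.** The best defence is that Sample size contains the only formal hypothesis, so dose-taking compliance is the primary test in practice. It is also listed first among the items, and the primary outcome is stated in the singular. On this view the plan is under-specified rather than contradictory, and testing order may sit in a full protocol or analysis plan that is not shown. Much of this stands. The sections can be read together, and the absence of a multiplicity procedure is not itself the finding. But the choice of primary variable is a protocol matter, and the article does state it, in a form that does not match its own sample size.

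A reader might infer more than the text supports:

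- **That each item is tested at 0.05.** The text does not say so. It is an inference from one general threshold and several items of equal rank. Nor does any section say that a win on any one item counts as success; the text simply does not exclude it.
- **That the period is open.** The formulas do use generic wording, such as "the number of pills taken over a certain time period". However, the Abstract says adherence is compared for the follow-up period, which is 6 months. The window is only not carried into the endpoint definition.
- **That testing at six visits inflates the error further.** The visit schedule attaches to the counts ("pill counts are done at 4, 8, 12, 16, 20, and 24 weeks of follow-up"), and Statistical analysis presents visit data as summary statistics. No between-group test by visit is specified.
- **That 18.5% or 22.6% is the expected size.** Independence is not credible for items drawn from the same dosing record: a day without doses lowers all three compliance measures and counts as a drug holiday. The five-item figure also treats medication possession ratio as a primary test, which the list of assessed items does not support.

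**Conclusion.** The point holds. The article leaves open which of four equally ranked items decides the trial, while its hypothesis and sample size rest on one. Followed as written, the plan allows the false-positive rate of the primary claim to exceed 5%: about 9% to 14% for four items at assumed correlations of 0.9 to 0.5, with 18.5% as the ceiling for items that are not negatively correlated. These figures depend on separate one-sided tests at 0.05, which is inferred, and on correlations that the document does not give. The direction depends on no particular correlation, since the rate exceeds that of a single test whenever the correlation is below 1. The mismatch between four named items and five formulas is a smaller inconsistency in the same section.

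**What to change.** In Primary outcomes and Statistical analysis, name dose-taking compliance over the full follow-up (randomisation to week 24, in line with the Abstract), one value per patient, as the single primary endpoint, tested at the stated alpha. Move dose-frequency compliance, dose-interval compliance, drug holidays and medication possession ratio to Secondary outcomes, and make the list of items match the list of formulas.

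This is a change of wording. Alpha and sample size are unchanged. The downside is that the other adherence items no longer carry a primary claim. If the sponsor wants them to, the Bonferroni figures above show the approximate price: 88 per group instead of 57 for four items. Either way, the choice should be recorded before any between-group adherence comparison is made, particularly because the trial is open-label.
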